## Abstract

**Background:**

Venous thromboembolism (VTE) is a common and severe complication during treatment of acute lymphoblastic leukemia (ALL). An important cause is the intensive use of asparaginase. Prospective cohort studies in which prophylactic low-molecular-weight heparin (LMWH) was used to prevent VTE showed lower VTE risk than in historic control cohorts, with a negligible bleeding risk. However, the efficacy of thromboprophylaxis with LMWH during ALL treatment has never been investigated in a randomized design. Here, we present the protocol of a randomized controlled trial in which the efficacy and safety of thromboprophylaxis with high prophylactic dose LMWH versus no thromboprophylaxis will be assessed in children treated for primary ALL with asparaginase.

**Methods/Design:**

Thromboprophylaxis in Children treated for Acute Lymphoblastic Leukemia with Low-molecular-weight heparin (TropicALL) is a multicenter, randomized controlled open-label trial conducted in the Netherlands. Patients between 1 and 19 years of age with primary ALL, who are treated within the Dutch Childhood Oncology Group (DCOG) ALL-11 or 12 study will be randomized to thromboprophylaxis with LMWH once daily, (dose of 85 IU/kg (intervention arm A)), or to no thromboprophylaxis (arm B, standard of care) during asparaginase courses of ALL treatment. Primary efficacy endpoint is symptomatic objectified VTE during ALL treatment; secondary efficacy endpoints are overall survival and the composite of symptomatic and asymptomatic objectified VTE. Primary safety endpoints are major bleeding, clinically relevant non-major bleeding and minor bleeding. A total of 324 patients will be included to obtain a relative risk reduction of 75% with a power of 80%, using a two-sided test with significance level α = 0.05.

**Discussion:**

This trial will be the first to assess efficacy and safety of thromboprophylaxis with LMWH during asparaginase treatment for ALL in children in a randomized design.

**Trail registration:**

Nederlands Trial Register NTR4707. Registered 30 July 2014.

## Background

Acute lymphoblastic leukemia (ALL) is the most common type of childhood cancer, representing a quarter of all pediatric malignancies [1, 2]. Survival rates for childhood ALL have improved significantly over the past decades, with a current 5-year survival of 86% [3, 4]. This is a result of substantial improvements in ALL treatment with risk-based therapy, increased treatment intensity and improved supportive care [5, 6].

Venous thromboembolism (VTE) is a frequent and severe complication during ALL treatment. Reported incidences of VTE during ALL treatment vary from 1 to 37% [7]. In unpublished data of the most recent Dutch Childhood Oncology Group (DCOG) ALL study, the ALL-10, incidence of symptomatic VTE was about 10% [3], but may have been underreported as VTE events were not systematically registered. The majority of VTE during ALL treatment are cerebral sinovenous thrombosis (CSVT) and catheter-related deep-vein thrombosis (DVT) (35–43%) [7–10]. CSVT can be severe and life-threatening [7, 8]. Reported overall mortality of CSVT varies between 10 and 21%, however limited data are available [7, 11]. Long term complications are common; more than 50% of patients with CSVT suffer from persistent neurological or cognitive impairments, and one fifth of patients has a reported poor quality of life [12–15]. Although mortality is rare in other types VTE such as (catheter-related) DVT, morbidity is frequent with for instance post-thrombotic syndrome (PTS), characterized by swelling, ulceration, pain and dilated collateral veins of the affected limb due to hampered venous flow, being frequently seen, with reported in up to 68% of patients [16–19].

Risk factors for VTE in ALL patients are well described but difficult to avoid. In particular, asparaginase therapy, which is an important component of ALL therapy, is considered to be a major risk factor for VTE as it reduces levels of natural anticoagulant proteins. Concomitant administration of corticosteroids may amplify this effect [7, 8, 20, 21]. In addition, a procoagulant state at diagnosis, presence of central venous catheters (CVCs), inherited prothrombotic defects and infections contribute to the risk of VTE [7, 8, 20, 22].

VTE occurrence leads to suboptimal treatment of ALL patients. In 68% of CSVT patients, therapy adjustments are necessary [11], which may lead to reduced survival rates [4]. In addition, CVC-related DVT is associated with recurrent catheter complications, such as obstruction of the catheter and catheter-related infections [23].

Currently, there are no evidence-based strategies to prevent VTE complications during ALL treatment. Administration of fresh frozen plasma (FFP) or antithrombin (AT) do not reduce the risk of VTE [24]. A few prospective cohort studies have been published which use low-molecular-weight heparin (LMWH) for thromboprophylaxis during ALL treatment. Elhasid et al. reported on 41 children with ALL who received LMWH prophylaxis during 4 to 8 courses in18–24 days of L-asparaginase treatment. During 76 courses of asparaginase, none of the children developed VTE and no bleeding episodes occurred [25]. Mitchell et al. described 19 children with ALL and increased risk for thrombosis, based on a VTE-risk score, including asparaginase, steroids, presence of CVC and thrombophilia. VTE developed in 1 of 8 children who were given prophylactic dose LMWH and in 8 of 11 children without thromboprophylaxis. No bleeding events occurred [26].

However, thromboprophylaxis with LMWH during ALL treatment has not been studied in a randomized design. As the prospective cohort studies showed promising results with a negligible bleeding risk, a large randomized controlled trial is needed to confirm these findings.

## Methods

### Aim and study design

The TropicALL study is a multicenter randomized controlled open-label trial conducted in the Netherlands. The aim of this study is to assess the efficacy and safety of thromboprophylaxis with LMWH in children treated for primary ALL in the DCOG ALL-11 or subsequent study. As a secondary objective, clinical risk factors will be evaluated to increase insight in the pathogenesis of VTE during ALL treatment and to establish a risk model for these complications. In addition, since a thrombophilic state is associated with a higher VTE risk, specific coagulation assays, including antithrombin, fibrinogen, D-dimer, thrombin antithrombin complex (TAT) and thrombin generation, and genetic thrombophilic mutations Factor V Leiden and prothrombin G20210A will be performed in patients with and without VTE. The inclusion period is 3 years with a follow-up of 3 months after the end of the ALL treatment period, or until recurrence of ALL, or until death. Primary efficacy endpoint is the incidence of symptomatic objectified VTE during ALL treatment; secondary efficacy endpoints are incidence of the composite of symptomatic and asymptomatic objectified VTE, and the value of plasma coagulation assays to predict the risk of VTE. Primary safety endpoint is major bleeding. Secondary safety endpoints are the incidence of clinically relevant non-major bleeding and minor bleeding, the burden of LMWH injections, and adverse skin reactions.

Patients will be closely monitored for adverse events during the study. All serious adverse events and unexpected adverse reactions, will be reported through the web portal ToetsingOnline to the accredited Ethics Committee that approved the study protocol. Furthermore a Data Monitoring Committee will semi-annually review all incidences of adverse events, symptomatic VTE and bleeding complications. To enhance safety of the study, DMC will provide the core committee with recommendations related to the protection of the patients’ safety, including stopping recruitment and study treatment.

### Definitions

Symptomatic VTE is defined as suspicion of VTE based on clinical symptoms, for instance for (CVC-associated) DVT: peripheral deep vein thrombosis, swelling, erythema, skin discoloration, increased warmth, pain, tenderness, venous distension, or presence of subcutaneous collateral veins and objectively confirmed by imaging tests. Other forms of VTE (i.e. pulmonary emboli and CSVT) are defined as symptomatic venous thrombosis in any component of the venous or pulmonary arterial circulations or the heart, or the cerebral sinovenous system, requiring therapeutic anticoagulation, acute intervention, life-saving measures, ALL treatment adjustments, or of fatal nature, and objectively confirmed by routine imaging tests. Screening for asymptomatic VTE should not be performed. However, if thrombi are incidentally found upon diagnostic imaging for other indications, these are counted as asymptomatic VTE. Treatment of these asymptomatic VTE will be determined by the attending physician.

Bleeding is categorized as major, clinically relevant non-major or minor bleeding according to Perinatal and Pediatric Subcommittee of the Scientific and Standardization Committee of the International Society on Thrombosis and Haemostasis criteria [27]. A bleeding is considered as major if it is a fatal bleeding, clinically overt bleeding associated with a decrease in hemoglobin of at least 3.1 mmol/l in a 24-h period, bleeding that is retroperitoneal, pulmonary, intracranial, or otherwise involves the central nervous system; and bleeding that requires surgical intervention in an operating suite. A clinical relevant non-major bleeding is defined as an overt bleeding for which a blood product is administered and not directly attributable to the patient’s underlying medical condition or a bleeding that requires medical or surgical intervention to restore hemostasis, not in an operating suite. All other overt bleedings or macroscopic evidence of bleeding are considered minor.

Burden of LMWH injections is estimated by a visual analogue scale (VAS) score and defined as a VAS score > 5.

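### The haemoglobin criterion for major bleeding (3.1 mmol/L in 24 h) equals about 5 g/dL, is nearly unattainable in anaemic children, and so under-counts major bleeding; it should be checked against its source

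*Protocol article*

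**What the plan says.** Under Definitions, the Protocol article grades bleeding as major, clinically relevant non-major (CRNM) or minor, and attributes the grading to published paediatric criteria cited as reference 27. There are four routes to major:

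- death: "A bleeding is considered as major if it is a fatal bleeding";
- haemoglobin: "clinically overt bleeding associated with a decrease in hemoglobin of at least 3.1 mmol/l in a 24-h period";
- site: "bleeding that is retroperitoneal, pulmonary, intracranial, or otherwise involves the central nervous system";
- surgery: "bleeding that requires surgical intervention in an operating suite".

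Only the second involves haemoglobin. There are two routes to CRNM. One is "an overt bleeding for which a blood product is administered and not directly attributable to the patient’s underlying medical condition". The other is a bleed that needs medical or surgical treatment to stop it, outside an operating suite. For the rest: "All other overt bleedings or macroscopic evidence of bleeding are considered minor".

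Aim and study design states: "Primary safety endpoint is major bleeding", with CRNM and minor bleeding as secondary. Statistical analysis instead takes major and CRNM bleeding together as the primary safety outcome, and the Abstract lists all three grades as primary. Treatment arms in TropicALL and Safety measures both make actions depend on major bleeding.

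**The concern.** The article prints the threshold in mmol/L only. It does not say which haemoglobin molecule the mole refers to, and it gives no equivalent in g/dL. Once converted, the required fall is very large for children in leukaemia treatment, who are randomized on day 11 of induction and may be thrombocytopenic, since thrombocytopenia does not exclude them.

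The definition also makes no mention of red cells transfused during the 24 hours, while Safety measures names transfusion among the usual treatments for bleeding. Treating the bleed can therefore prevent the fall that would classify it.

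At stake is the main safety comparison of an anticoagulant with no anticoagulant. If LMWH causes extra bleeds of the kind that only the haemoglobin route could make major, the absolute excess of major bleeding on LMWH is understated. The same term also governs actions in two other sections.

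**Working it through.** **Inputs.** The threshold of 3.1 mmol/L in 24 h is from Definitions. The molar masses are standard constants, not in the article: 16.114 g/mmol for the monomer and 64.458 g/mmol for the tetramer. Starting haemoglobin is an assumption, because the article gives no values; I use 7 to 12 g/dL. The article does not derive 3.1 mmol/L, so there is no calculation of its own to reproduce.

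**Step 1: conversion.** g/dL = mmol/L × molar mass / 10.

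- Monomer: 3.1 × 16.114 / 10 = 4.995, or 5.0 g/dL.
- Tetramer: 3.1 × 64.458 / 10 = 19.98, or 20 g/dL. This exceeds every starting value considered here, so such a fall cannot occur.

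Only the monomer reading can be met at all, and the rest uses it.

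**Step 2: share of starting haemoglobin.** Share = 4.995 / starting value; end value = starting value − 4.995.

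| Assumed start (g/dL) | Start (mmol/L, monomer) | Share lost | End (g/dL) |
|---|---|---|---|
| 7 | 4.34 | 71% | 2.0 |
| 8 | 4.96 | 62% | 3.0 |
| 9 | 5.59 | 56% | 4.0 |
| 10 | 6.21 | 50% | 5.0 |
| 12 | 7.45 | 42% | 7.0 |

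The required loss is half or more when the starting value is 10 g/dL or less.

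**Step 3: where a bleed below the threshold goes.** Take an overt gastrointestinal bleed with a fall of 2.5 mmol/L (2.5 × 1.6114 = 4.03 g/dL) in 24 h. It is not fatal and is not operated on in an operating suite, and its site is not on the critical list. It is not major. Its grade then depends on management and attribution:

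- blood product given, bleed not attributed to the underlying condition: CRNM;
- treatment needed to stop the bleed, outside an operating suite: CRNM, with or without a blood product;
- blood product given, bleed attributed to the underlying condition, no other haemostatic treatment: minor;
- neither blood product nor haemostatic treatment: minor.

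**Step 4: effect on each version of the primary safety endpoint.** With major bleeding alone (Aim and study design), all four cases are lost. With major or CRNM bleeding (Statistical analysis), the first two are kept and the last two are lost. With all three grades (Abstract), every event is counted, though its severity grade is still too low.

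**The case against.** The strongest reply is that haemoglobin is only one of four routes to major. Fatal bleeds, bleeds at the listed critical sites and bleeds operated on in an operating suite stay major whatever the haemoglobin. The second CRNM route catches bleeds that need haemostatic treatment even when no blood product is given, and Statistical analysis counts CRNM bleeding in the primary safety outcome. All of this is correct, and it limits the damage. A reader might infer that most serious overt bleeds will be missed. The article does not support that: it gives no distribution of bleed types from which a proportion could be derived.

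A reader might also infer that the Data Monitoring Committee would be misled. That is not supported either. Under Aim and study design the committee reviews bleeding complications of every grade twice a year, so it would see these events, although under a lower label.

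Next, the threshold of the cited criteria is not in the article. It is tempting to infer what number was intended and by what factor the printed one is off. Without the source neither can be said, and an error in transcription or units remains a suspicion.

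Finally, the starting values are assumed. Day 11 of induction is also only part of the exposure: medium-risk patients, 70% of the total, receive LMWH for 34 weeks including intensification. A child starting at 12 g/dL needs a 42% fall, not half. This is fair, but a 42% loss within one day is still an extreme requirement.

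The conversion itself is not disputed by any of this, nor is the grading that follows from it.

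**Conclusion.** The point holds in a limited form. The printed criterion means a fall of 5.0 g/dL in 24 h in the only convention in which it can be met. That is 42% to 71% of all haemoglobin for assumed starting values of 12 down to 7 g/dL. In anaemic children the haemoglobin route is close to inoperative, and transfusion for the bleed makes it more so.

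The consequence is confined to overt bleeds with a large haemoglobin loss that qualify as major by no other route. These are under-graded, so major bleeding is under-counted as the primary safety endpoint in Aim and study design. The composite in Statistical analysis recovers those graded CRNM but not those that fall to minor. How many events this concerns cannot be estimated from the article.

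The conclusion rests on the monomer conversion and on the assumed range of starting haemoglobin. It does not depend on what the cited criteria say; the correct replacement value does.

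**What to change.** 1. Check 3.1 mmol/L and its unit convention against the criteria cited as reference 27, and correct the endpoint threshold to that source.
2. Print the threshold in both mmol/L and g/dL, and name the convention (monomer or tetramer).
3. Re-grade bleeds already recorded wherever haemoglobin values are available. Data and blood sample collection does not list haemoglobin among the items collected, so availability has to be confirmed first.
4. Reconcile Treatment arms in TropicALL and Safety measures with the corrected definition, because LMWH interruption and the bleeding measures depend on the same term. No clinical rule is proposed here.

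The cost is a short amendment to one definition and the re-grading work. The small downside is that more bleeds may count as major, so the safety profile may look slightly less favourable.

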### Study population

Children between 1 and 19 years of age with primary ALL, who are treated within the DCOG ALL-11 or subsequent study, are eligible for the TropicALL. Patients will be excluded if they are already using anticoagulant therapy upon screening, if they have active bleeding or a high risk for bleeding contraindicating anticoagulant therapy, including renal insufficiency (glomerular filtration rate (GFR) < 30 ml/min/1.73 m2), hepatic disease associated with coagulopathy leading to a clinically relevant bleeding risk, stage 2 hypertension defined as blood pressure confirmed >99th percentile +5 mmHg, if they have a heparin allergy or a history of heparin-induced thrombocytopenia (HIT), or any other condition that, judged by the investigator, would place the patient at increased risk of harm due to participation. Thrombocytopenia is no exclusion criteria. However, LWMH should be temporarily interrupted, if platelet levels drop below 20 × 10^9^/L.

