### Statistical analysis

All data will be analyzed according to the intention-to-treat principle. Descriptive data will be presented as mean with its corresponding standard deviation if normally distributed, and medians with ranges if data are skewed. Depending on the data distribution the Student’s *t* test or a Mann-Whitney U-test will be used to compare continuous variables between the treatment groups. Categorical variables will be analyzed using the Chi-square test.

Efficacy and safety of LMWH to prevent VTE will be analyzed by the difference between the incidence proportions and cumulative incidences of the primary efficacy and safety outcomes, symptomatic objectified VTE and major or clinically relevant non-major bleeding, respectively, observed from randomization up to 14 and 7 days after the last PEG asparaginase and Erwinia asparaginase, respectively. A two-sided test with significance level α = 0.05 will be used.

All bleeding events that occur during LMWH or within 2 days after cessation of LMWH will be included. Incidence proportions (number of children with outcome during the period divided by number of children at risk at the beginning of the period) and cumulative incidences will be estimated by a joint model to estimate event free survival for the primary safety outcome. To identify which risks factors are associated with time to VTE a joint model for longitudinal data and survival outcome will be used.

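### One route to clinically relevant non-major bleeding turns on a causal judgement that can differ by arm in this open-label trial; an attribution-free count should be reported beside it

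*Protocol article*

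**What the plan says.** The Definitions section of the protocol article grades bleeding in three levels and presents them as published criteria: "Bleeding is categorized as major, clinically relevant non-major or minor bleeding according to Perinatal and Pediatric Subcommittee of the Scientific and Standardization Committee".

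- **Major** bleeding rests on facts such as a fatal outcome, a critical site, surgery in an operating suite, or "clinically overt bleeding associated with a decrease in hemoglobin of at least 3.1 mmol/l in a 24-h period". No causal judgement is asked for.
- **CRNM**, first route: "an overt bleeding for which a blood product is administered and not directly attributable to the patient’s underlying medical condition".
- **CRNM**, second route, joined as an alternative: "or a bleeding that requires medical or surgical intervention to restore hemostasis, not in an operating suite". It has no attribution clause.
- **Minor** is the remainder: "All other overt bleedings or macroscopic evidence of bleeding are considered minor".

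Aim and study design describes a "multicenter randomized controlled open-label trial conducted in the Netherlands", and Treatment arms in TropicALL gives arm B no thromboprophylaxis at all. Under Study population, "Thrombocytopenia is no exclusion criteria", and LMWH is interrupted when platelets fall below 20 × 10^9/L.

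The standing of the CRNM grade varies. Aim and study design makes major bleeding the primary safety endpoint and CRNM a secondary one. The Statistical analysis section names the primary efficacy and safety outcomes as "symptomatic objectified VTE and major or clinically relevant non-major bleeding, respectively". The Abstract lists all three grades as primary safety endpoints.

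**The concern.** The attribution clause asks whether the underlying condition caused the bleed. In arm A there is a visible competing explanation, the anticoagulant. In arm B that explanation is absent by design, while leukaemia is present in every child. The answer is therefore tied to treatment arm, and an assessor who knows the arm can in good faith answer differently for two similar bleeds. An assessor with a view on LMWH could also lean either way.

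At the margin, the answer decides whether a bleed counts in the compared outcome or drops to minor. Analysis by intention to treat keeps children in their randomized arm but does not correct outcome classification that depends on the arm. The result could be an apparent excess of bleeding with LMWH that is not real, or a real excess that is hidden. The Discussion says the results are meant to support guidelines, so the bleeding side of the balance matters.

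**Working it through.** **1. Which bleeds the clause can move.** Follow a non-major overt bleed for which a blood product was given.

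| Second route (intervention to restore haemostasis) met? | Judged directly attributable to underlying condition? | Grade |
|---|---|---|
| Yes | Either | CRNM |
| No | No | CRNM |
| No | Yes | Minor |

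Only the last two rows depend on attribution. The affected group is transfused, non-major bleeds that do not meet the second route. The article does not say whether platelets given to stop a bleed are themselves an intervention to restore haemostasis. If they are, such a bleed is CRNM in both arms and the clause does not matter for it.

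**2. The plan's own figure.** The only design number is the sample size for VTE: 10% against 2.5% (a 75% relative reduction), two-sided α = 0.05, power 80%. With pooled variance and mean proportion 0.0625:

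n = [1.960·√(2 × 0.0625 × 0.9375) + 0.842·√(0.10 × 0.90 + 0.025 × 0.975)]² / 0.075² ≈ 162.3

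Rounded up this is 163, against the stated 162; power at 162 is 79.9%. The figure is reproduced, and bleeding grades do not enter it.

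**3. Illustration (all rates assumed).** Let r be the same true proportion in each arm with a bleed in the affected group. Let qA and qB be the shares judged not attributable to the disease. Expected CRNM counts from this group are 162·r·qA and 162·r·qB, and their ratio is qA/qB. The chance of a two-sided p < 0.05 is from the normal approximation for two proportions, which is rough at the smaller counts.

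| r | qA / qB | Expected CRNM, A v B | Risk ratio | Chance of p < 0.05 |
|---|---|---|---|---|
| any | 50% / 50% | equal | 1.0 | 5% |
| 5% | 60% / 40% | 5 v 3 | 1.5 | 9% |
| 10% | 60% / 40% | 10 v 6 | 1.5 | 13% |
| 20% | 60% / 40% | 19 v 13 | 1.5 | 22% |
| 5% | 75% / 25% | 6 v 2 | 3.0 | 30% |
| 10% | 75% / 25% | 12 v 4 | 3.0 | 54% |
| 20% | 75% / 25% | 24 v 8 | 3.0 | 85% |

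Example: 162 × 0.10 × 0.75 = 12.15 and 162 × 0.10 × 0.25 = 4.05. Exchanging the two shares gives the mirror image, an apparent deficit in arm A.

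**4. Effect of the second route.** If a share h of transfused non-major bleeds meets the second route in both arms, the ratio becomes [h + (1 − h)qA] / [h + (1 − h)qB]. At 75% against 25%, h = 0 gives 3.0, h = 0.5 gives 0.875/0.625 = 1.4, and h = 1 gives 1.0. The table in step 3 is therefore the upper end for each split.

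**The case against.** The strongest reply is that the clause is presented as part of published consensus criteria. Using them is a standard choice and neither an error nor an internal contradiction, and a home-made main definition would cost comparability with other trials. That stands, and it is why the fix adds an analysis and leaves the definition in place.

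Other points also stand in whole or in part.

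- A reader might infer that a transfused bleed can reach CRNM only through the attribution judgement. The definition does not say so: the second CRNM route and the major grade both bypass it. A nosebleed treated with platelets could well be CRNM in both arms.
- A reader might infer that the unblinded treating clinician assigns the grade. The article names no assessor. Masked adjudication could be set out in the full protocol or a charter, which are not shown, and its absence from an article is no fault. Masking would, however, have to cover LMWH exposure to neutralise this clause.
- The text speaks of the underlying medical condition. Whether thrombocytopenia caused by chemotherapy belongs to it is not stated, so one cannot assume that arm B bleeds would routinely fail the clause.
- Aim and study design makes major bleeding primary, and that grade carries no attribution clause. This limits the reach of the problem, although CRNM is a compared safety outcome under every version in the article.
- The assumed rates have no anchor. Both LMWH cohorts described in the Background reported no bleeding.
- An attribution-free count does not remove all dependence on open-label care, since the decision to transfuse or intervene is also made with the arm known. It removes one layer of judgement, not every one.

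None of this answers the narrow point that, for the affected group, the grade depends on a causal opinion tied to treatment arm.

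**Conclusion.** The concern holds in a limited form. The transfusion route to CRNM contains an attribution judgement that can differ by arm, and for transfused, non-major bleeds outside the second route it decides between CRNM and minor. This affects the combined bleeding outcome in the Statistical analysis section and the separate CRNM endpoint in Aim and study design. It does not affect major bleeding, the VTE comparison or the sample size.

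It is tempting to conclude that the definition will inflate bleeding with LMWH and deflate it in controls. The documents do not support a direction: it depends on who grades, what they know and how they read the clause. Nor do they support a size. The ratios of 1.5 and 3.0 rest on assumed attribution shares, equal true bleeding and no bleed meeting the second route; the chances of a significant result also rest on assumed bleed rates of 5% to 20%. This is a cheap improvement to make before analysis, not a flaw that undermines the trial.

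**What to change.** Keep the cited criteria as the main grading.

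1. Record, as separate CRF items for each overt bleed, any blood product given, the presumed attribution and the platelet count at the bleed.
2. Pre-specify a between-arm analysis that counts every overt bleed for which a blood product was given or an intervention outside an operating suite was needed, whatever the presumed cause. Leave major bleeding as defined. Report this count by arm next to the criteria-based one; if the two disagree, the bleeding difference depends on attribution and should be described so.
3. Reconcile the Abstract, Aim and study design, and Statistical analysis on whether CRNM bleeding belongs to the primary safety outcome.

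The cost is one extra analysis and one or two CRF fields. The downside is that background thrombocytopenic bleeds enter the added count in both arms and may dilute a true effect of LMWH, which is a reason to show both counts.
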